## Abstract

**Background:**

Very preterm infants (< 32 weeks gestation) have a relatively high nutrient requirement for growth and development. The composition of human milk is often inadequate to ensure optimal growth so it is common to fortify human milk for very preterm infants with nutrient fortifiers based on bovine milk. However, there are concerns that bovine milk-based fortifiers may increase the risk of feeding intolerance, necrotizing enterocolitis and late-onset sepsis. We hypothesize that a bovine colostrum-based product is a suitable alternative to bovine milk-based products when used as a fortifier to human milk in very preterm infants.

**Methods/Design:**

In an open-label multicentre randomised controlled pilot trial, 200 very preterm infants (26 + 0 to 30 + 6 weeks gestation at birth) will be randomly allocated to a bovine colostrum-based or a bovine milk-based fortifier added to mother’s own milk and/or human donor milk. Outcomes are growth rate, incidence of necrotizing enterocolitis and late-onset sepsis, a series of paraclinical endpoints, and practical feasibility of using the novel fortifier for very preterm infants.

**Discussion:**

The optimal enteral diet and feeding regimen for very preterm infants remain debated; this clinical trial will document the feasibility, safety and preliminary efficacy of using bovine colostrum, rich in nutrients and bioactive factors, as a novel fortifier for human milk to very preterm infants*.* Data on infant growth, metabolism, gut function and immunity will be assessed from clinical data as well as blood and stool samples.

**Trial registration:**

Registered retrospectively 25 May 2018 at ClinicalTrials.gov: NCT03537365.

**Electronic supplementary material:**

The online version of this article (10.1186/s13063-019-3367-7) contains supplementary material, which is available to authorized users.

## Background

Very preterm infants (< 32 weeks gestation) have a relatively high nutrient requirement for growth and development. Poor growth in the postnatal period is associated with later impaired neurodevelopment [1–3], metabolic disorders [4] and short stature [5]. Provision of adequate energy and nutrients (e.g. protein, minerals, vitamins) helps to prevent postnatal growth restriction [6]. Parenteral nutrition may initially be needed to support optimal nutrient intake in very preterm infants. Long-term parenteral nutrition is associated with higher risk of late-onset sepsis (LOS) [7], while a too fast increase in enteral nutrition may predispose to feeding intolerance and necrotizing enterocolitis (NEC) [8]. Further, excessive weight gain may predispose to metabolic and cardiovascular disorders later in life [9, 10]. It therefore remains a difficult task to optimize the transition to enteral nutrition, achieve adequate nutrient intake, minimise LOS and NEC, and achieve optimal growth in the postnatal period of very preterm infants [6, 7, 11].

Mother’s own milk is considered the best source of enteral nutrition for very preterm infants [12], and if mother’s own milk is not available or production is insufficient during the first weeks after preterm birth, human donor milk is recommended as the second choice. A protein intake of 3.5–4.5 g/kg/day is suggested for extremely and very preterm infants to achieve a postnatal growth rate similar to the intrauterine growth rate [13]. However, this recommended level of protein intake is seldom met by feeding on mother’s own milk and/or human donor milk alone. Furthermore, the amount of energy and protein varies widely in human milk both between mothers and throughout the lactation period [14, 15]. It has therefore become standard practice to enrich mother’s own milk and human donor milk with a nutrient fortifier to support growth, bone mineralization and neurodevelopment in very preterm infants [3, 16, 17].

Concerns have been raised that currently available fortifiers, based on bovine milk products derived from processed bovine milk and vegetable components, may increase feeding intolerance and the risk of developing NEC [18, 19]. A fortifier based on concentrated human donor milk has recently become available and very preterm infants fed exclusively human milk (mother’s own milk and/or human donor milk) fortified with the human donor milk product showed lower incidences of NEC and sepsis compared with infants fed diets partly or fully consisting of bovine-based products [20–22]. However, it remains unclear if bovine milk-based fortifiers (BMF) added to human milk (without any supplemental formula feeding) is a problem, and the high cost of the fortifier based on human milk may prevent its widespread use in the future [23]. A recent randomised control trial in preterm infants showed no difference in feeding tolerance when a human milk-based fortifier was compared with a bovine milk-based fortifier and vegetable products [24]. Fortifiers based on milk from non-bovine species are also being tested (e.g. donkey) to investigate whether bovine milk protein constitutes a specific problem for preterm infants [25].

Bovine colostrum (BC) is the first milk from cows after parturition and, like human colostrum, it contains much higher levels of protein, antimicrobial factors, immunoregulatory factors and trophic factors than mature milk (e.g. immunoglubolins, lactoferrin, lysozyme, lactoperoxidase, osteopontin, transforming growth factor, insulin-like growth factors, epidermal growth factor) [26]. These components may improve gut maturation, protection and nutrient assimilation, even across species. Used as the first feed or as a fortifier to human milk, intact BC improves gut maturation and NEC resistance in preterm pigs [27–29] and preliminary studies indicate that it is well tolerated also in preterm infants [30, 31].

On this background, we hypothesize that a powdered BC-based fortifier (BCF) for human milk can induce similar growth and better NEC and LOS resistance than a conventional, powdered BMF. A pilot trial is required to test the practical feasibility and safety of using BCF, e.g. that growth rates and clinical variables are similar to those of BMF. Further, the pilot trial is required to calculate the sample size for a later, larger randomised control trial with NEC and LOS as the primary outcomes.

## Methods/Design

### Study setting

This study is designed as an open-label randomised controlled multicentre pilot trial of BCF compared with a conventional BMF, both used to fortify human milk, i.e. mother’s own milk and/or human donor milk (Figs. 1 and 2).

**Fig. 1 Fig1:**
[figure not shown]
Flow of participants and data collection in the FortiColos Study

**Fig. 2 Fig2:**
[figure not shown]
SPIRIT figure for FortiColos showing the schedule of enrolment, interventions and assessments

### Study population

Study participants will be recruited from multiple neonatal intensive care units and neonatal care units in Denmark. Very preterm infants born between gestational age 26 + 0 and 30 + 6 weeks will be recruited if they are in need of nutrient fortification to achieve optimal growth rates, as judged by the responsible clinical personnel. The infant should stay at one of the participating units at least until postmenstrual age (gestational age plus weeks and/or days since birth) 34 + 6 weeks, before being transferred to a non-participating unit. Infants participating in an early discharge programme (discharged home for breastfeeding establishment with a nasogastric tube) can also participate in the study until discharged. Exclusion criteria are major congenital anomalies and birth defects, gastrointestinal surgery and formula feeding prior to randomisation.

### Intervention

Introduction of enteral nutrition will follow the standard practice at the participating neonatal care unit and neonatal intensive care units. At all units, the mothers are encouraged to express breast milk as soon as possible after birth and continue expressing, so the infants will receive as much mother’s own milk as possible. Human donor milk will be used when mother’s own milk is not available or insufficient in amount. Fortification of human milk (both mother’s own milk and/or human donor milk) will start when enteral nutrition reaches a volume of at least 100 and maximum 140 mL/kg/day, unless blood urea nitrogen (BUN) values are > 5 mmol/L. In such cases, fortification may be delayed and started at higher feeding volumes. Eligible infants will be randomly assigned to one of two groups, namely human milk will be fortified with either BCF (Bovine colostrum, Biofiber, Gesten, Denmark) or a commercially available BMF (PreNAN FM85, Nestlé, Vevey, Switzerland). Table 1 shows the composition of macronutrients and bioactive components in BCF compared with the values in mature bovine milk, human colostrum, human term and preterm milk [32–39]. The control BMF fortifier is currently used for very preterm infants at all Danish neonatal units. The nutrient compositions of the two fortifiers are compared in Table 2. On the first day of intervention, 1.0 g of fortification is added to 100 mL of human milk in both groups. In the following days, the amount of BCF and BMF is upregulated with a planned speed to ensure that the same protein level is provided from both fortifiers to a maximum of 1.4 g per 100 mL of human milk, corresponding to 2.8 g of BCF and 4.0 g of BMF. The units may choose to individualise the fortification level according to the amount of protein in mother’s own milk measured on a weekly basis, or they may use standard fortification based on an assumed composition of human milk [15]. The infants will receive fortified human milk as long as additional protein is needed, according to postnatal growth rates and breastfeeding establishment. Both groups will be supplemented with phosphorus, iron, multivitamins and vitamin D according to standard recommendations.

**Table 1 Tab1:** Macronutrient composition and bioactive factors in bovine and human colostrum, term and preterm milk

	Bovine colostrum	Human colostrum	Preterm human colostrum	Term bovine milk	Term human milk	Preterm human milk
Protein, g/L	60–135^a^	11–32^c^	19^f^	34^c^	9–12^g^	12.7^f^
Casein, g/L	26^b^	3.0–5.6^c^		2~30^c^	4–4.8^g^	
Whey, g/L	35–119^a^	4.3–11.1^c^		4~50^c^	6–7.2^g^	
α-Lactalbumin, g/L	2.04^c^	2.56^c^		1–1.5^c^	2–3^c^	
β-Lactoglobulin, g/L	14.3^c^	None^c^		3–4^c^	None^c^	
Lactoferrin, g/L	1.0–2.0^c^	5.0–7.0^c^		0.01–0.1^c^	1.0–2.0^c^	
Immunoglobulins, g/L	20–150^c^	1.14–20^c^		0.6–1.0^c^	1.2^c^	
Lactoperoxidase, mg/L	11–45^c^	5.17^c^		13–30^c^	5.17^c^	
Osteopontin, mg/L	Not determined^c^	1493.4^c^		18^c^	138^c^	
Lysozyme, mg/L	0.14–0.7^c^	270–430^c^		0.07–0.6^c^	160–460^c^	
Superoxide dismutase, U/mL	0.06–2.88^c^	18.7–22.5^c^		0.06–2.88^c^	11.2^c^	
Platelet-activating factor-acetylhydroxylase, μg/L	None^c^	0.95–1.19^c^		None^c^	1.16–1.21^c^	
Alkaline phosphatase, μkat/L	6.84^h^	1.79^c^		4.49^c^	0.92^c^	
Transforming growth factor-β, μg/L	150–1150^c^	1366^c^		13–71^c^	953^c^	
Insulin-like growth-I, μg/L	49–2000^c^	29–49^c^		4–150^c^	3–6^c^	
Insulin-like growth-II, μg/L	400–600^c^	10.5^c^		50–100^c^	35^c^	
Epidermal growth factor, μg/L	4–324.2^c^	35–438^c^		2–155^c^	20–111^c^	
Lactose, g/L	18.9–32^a^	44–59^d^	57–74^f^	49^a^	67–78^g^	73^f^
Fat, g/L	50–80^a^	20–29^e^	26^f^	37^a^	32–3^g^	35^f^

^a^Abd El-Fattah AM [32], ^b^Korhonen HJ [33], ^c^Chatterton DEW [34], ^d^Espinosa-Martos I [35], ^e^Jensen RG [36], ^f^Boyce C [37], ^g^Ballard O [38], ^h^Zanker IA [39]

**Table 2 Tab2:** Amount of energy, protein, minerals and vitamins in PreNAN FM85 powder and the used bovine colostrum powder, as indicated when maximum fortification is reached

	Bovine colostrum Pr. 2.8 g	PreNAN FM85 Pr. 4.0 g
Energy, kcal	13	17
Protein, g	1.4	1.4
Carbohydrate, g	0.6	1.3
Fat, g	0.6	0.72
Calcium, mg	25.8	76
Phosphorus, mg	22.7	44
Zink, mg	0.20	0.96
Iron, mg	0	1.8
Vitamin D3, μg	0	3.5
Vitamin A, μg	27.8	333
Vitamin E, mg	0.05	3.8
Vitamin C, mg	0	19

### Data collection and management

We will collect data from birth until final discharge. During the intervention period, nurses will record information regarding feeding volumes, residuals (volume and colour), and appearance of stomach (any distension, colour and vessel appearance) and stools (amount, colour and texture), using a modified version of the Infant Stool Form Scale [40] and the COMFORTneo Scale [41]. Data will be collected using paper case report forms which are entered into an online database (REDCap) [42]. The electronic database is stored in a secure server at the Region of Southern Denmark.

Blood and stool samples will be collected before the first fortified meal, and at 1 and 2 weeks after start of fortification, and stored at − 60 °C to − 80 °C. All samples will subsequently be transported to a centralized biobank at the University of Copenhagen for later analysis. Randomised infants, discontinued early from the randomised type of fortification (according to clinical judgment or parental request, will with parental acceptance continue collecting data), will be considered as ‘off-study fortifier’ but ‘on study’ and followed until discharge with sampling of blood and faeces, if possible. Discontinuation due to withdrawal of parental consent or loss to follow-up will also be recorded.

### Outcome measures

#### Primary outcome

The primary clinical focus in this pilot trial is the evaluation of both body growth and incidence of NEC and LOS. The proposed primary outcomes in a later larger-scale randomised controlled trial will be NEC- and LOS-free survival, but this pilot study does not allow for a full investigation of these endpoints with adequate statistical power. Since the main reason to fortify human milk is to improve postnatal growth rates, it will also be important to document whether the novel BCF fortifier can induce infant growth rates similar to those of the conventional BMF. Body growth will be recorded as weight gain in grams from birth to discharge from hospital. Weight at different time points will be calculated into z-scores according to Niklasson and Albertsson-Wikland [43]. Delta z-scores will be used to evaluate growth and for comparison between groups. NEC is defined as Bell’s stage II or above [44]. LOS is defined as clinical signs of infection (e.g. increased heart rate, increased need of oxygen and episodes with apnoea, fluctuation of temperature and/or pale colour of the skin) with or without increased CRP after age 2 days, and antibiotic treatment for ≥ 5 days, or shorter if the infant died, with or without one positive bacterial culture in blood or cerebral spinal fluid.

#### Secondary outcomes

A series of secondary outcomes will be evaluated at different time points. Days on parenteral nutrition are defined as number of days the infant receives intravenous intakes of protein and/or lipid and/or glucose. Feeding volume when fortification is initiated, amount of fortification at each meal and duration of fortification will be registered. Time to reach full enteral nutrition (in days) is defined as the time when at least 150 mL/kg/d is reached and parenteral nutrition has been discontinued. Feeding intolerance is defined as proportion of days with a nutrition volume less than 50% of the total planned volume per day, measured during intervention. Stomach, residuals and stool appearance will be evaluated each day during intervention. Length of hospital stay is defined as days from birth until final discharge. Body length and head circumference will be measured from birth and once a week during intervention and at final discharge. BUN, blood minerals and blood haemoglobin will be collected from medical records during the intervention period. Plasma levels of amino acids, intestinal fatty acid binding protein, neutrophil extracellular trap components, lactoferrin and interleukin (IL) will be measured prior to and 1 and 2 weeks after start of fortification. Faecal composition of microbiota and faecal levels of IL-8, calprotectin (S100-A8/9) and metabolites (short-chain fatty acids) will be measured in faecal samples taken just prior to and 7 and 14 days after start of fortification.

### Randomisation and blinding

Each infant will be randomly allocated by a local member of the research team who accesses an online randomisation programme (REDCap) via a server at the Region of Southern Denmark. A computer-generated randomisation sequence will be used with a 1:1 allocation, random block sizes of 4–6, and stratified by small-for-gestational-age (SGA, yes/no), where SGA is defined as a birth weight z-score less than two standard deviations [44]. The random allocation sequence will be generated by an external data manager not involved in the trial. In case of multiple births, all siblings will be allocated to the same group, randomised by the first-born infant. Blinding is not possible in this trial, and the two powdered fortifiers can be distinguished by colour and texture. The schedule of enrolment, intervention and data collection are described in Figs. 1 and 2.

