### Statistical analysis

#### Sample size

The sample size in this pilot trial is set at *n* = 100 for each group (total 200) based on pragmatic evaluations for comparison between groups on infant growth, laboratory outcomes (clinical and paraclinical) and the study feasibility outcomes. If the primary endpoint had been NEC- and LOS-free survival, the total sample size should have been 1498 participants according to a power calculation, based on an aim to test a 50% reduction in NEC incidence and a 25% reduction in LOS incidence at discharge with 80% power and a two-sided 0.05 level of significance, and assuming a NEC incidence of 6% and a LOS incidence of 30%.

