#### Analysis

Statistical analyses will be performed as both intention-to-treat and per protocol analyses. Per protocol analysis will include infants treated with the randomised type of fortifier for a minimum time of 2 weeks. Continuous outcomes will be summarized as mean and standard deviation (e.g. body weight) or median and interquartile range (e.g. time to reach full enteral nutrition). Binary outcomes (e.g. incidence of NEC) will be presented as counts and percentages.

To make a preliminary test of the effects of the intervention with BCF, clinical and paraclinical outcomes will be compared between the two groups. The estimates will be presented as relative risk and absolute risk difference, difference between means or hazard ratio, depending on the type of outcome. The estimates will be presented with a 95% confidence interval. Regression models, logistic regression for binary outcomes and Cox regression for time to event outcomes will be used to evaluate the outcomes of interest between the two groups, adjusting for SGA (stratification variable) and covariates that are known to be prognostic in relation to the outcome variable (e.g. gestational age, birth weight and sex). A Fine–Gray regression, taking competing risk of infant death into account, will be carried out as a sensitivity analysis for time to event outcomes. If relevant, sensitivity analyses will be conducted using multiple imputations to explore the potential impact of missing data. Results from all these analyses will be considered preliminary since this a pilot-scale trial. The feasibility of the study will be presented as categorical variables with three levels as displayed in Table 3.

**Table 3 Tab3:** Pre-defined criteria used to decide whether, or how, to proceed with a later, larger randomised control trial. Green colour: Fully acceptable and feasible. Yellow colour: Feasibility concern, changes to be decided. Red colour: Serious feasibility concerns, clear actions must be taken before a greater randomised control trial is planned

			
Consent rate	> 70%	50–70%	< 50%
Recruitment rate	> 50%	20–50%	< 20%
Proportion of incomplete datasets	< 20%	20–50%	> 50%

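### Siblings are allocated together, but the models named for the between-arm comparisons make no allowance for family, so the 95% intervals would be somewhat too narrow

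*Protocol article*

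**What the plan says.** **Allocation.** The Randomisation and blinding section of the protocol article says "A computer-generated randomisation sequence will be used with a 1:1 allocation", stratified by SGA. It then adds: "In case of multiple births, all siblings will be allocated to the same group, randomised by the first-born infant". The Study population section does not exclude multiples.

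**Unit counted.** The sample is counted in infants. The abstract says "200 very preterm infants (26 + 0 to 30 + 6 weeks gestation at birth) will be randomly allocated", and the Sample size section sets 100 "for each group (total 200) based on pragmatic evaluations for comparison between groups on infant growth".

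**Analysis.** The Analysis section names regression models, logistic regression for binary outcomes, Cox regression for time-to-event outcomes, and a Fine–Gray sensitivity analysis. It allows for multiple imputation if relevant. Estimates carry 95% confidence intervals. The models are run "adjusting for SGA (stratification variable) and covariates that are known to be prognostic in relation to the outcome variable", with gestational age, birth weight and sex as examples. The section mentions no family term, random effect, GEE or clustered variance. It describes all results as preliminary.

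**The concern.** The analysis should reflect how infants were randomised. Two design features bear on it: stratification by SGA and joint allocation of siblings. The Analysis section carries the first into the models and not the second.

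Siblings share a mother and a gestational age, and usually her milk, so their growth, stool and plasma results are likely to be positively correlated. When both members of a pair are always in the same arm, that correlation inflates the variance of the arm mean. Models that treat each infant as a separate observation do not see this, and their standard errors come out too small.

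Two uses of the pilot are affected. It is meant to show whether growth on the colostrum fortifier is similar to growth on the control product, and intervals that are too narrow overstate how closely the arms have been shown to agree. The Background section also says that the pilot is needed to calculate the sample size of the later trial. An analysis that ignores family gives that calculation no estimate of the correlation between siblings.

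**Working it through.** **1. The plan's own figure.** The pilot's 200 is pragmatic, so it has no calculation to reproduce. The Sample size section does give 1498 for a later trial, "with 80% power and a two-sided 0.05 level of significance", with NEC at 6% reduced by half to 3%. The two-proportion formula for independent infants (pooled variance, no continuity correction) is

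n per arm = [1.96·√(2·0.045·0.955) + 0.842·√(0.06·0.94 + 0.03·0.97)]² / 0.03².

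This rounds up to 749 per arm, or 1498 in total, an exact match. The figure contains no allowance for siblings.

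**2. Inputs for the pilot.** N = 200 infants (Sample size section). Two quantities are not in the document and are assumed:
- s, the share of infants enrolled together with a twin: 10–40%
- ρ, the within-pair correlation of the outcome: 0.1–0.7

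**3. Formulas** for pairs always placed in the same arm:
- design effect D = 1 + s·ρ
- effective N = 200 / D
- correct interval width relative to the unadjusted one = √D
- actual error rate of a nominal two-sided 5% comparison = 2·[1 − Φ(1.96/√D)]

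**4. Results.**

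| s | ρ | D | Effective N | Correct interval wider by | Nominal 5% runs at |
|---|---|---|---|---|---|
| 0.1 | 0.1 | 1.01 | 198 | 0.5% | 5.1% |
| 0.2 | 0.3 | 1.06 | 189 | 3% | 5.7% |
| 0.3 | 0.5 | 1.15 | 174 | 7% | 6.8% |
| 0.4 | 0.7 | 1.28 | 156 | 13% | 8.3% |

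For the central row, 1 + 0.3·0.5 = 1.15, 200/1.15 = 174 and √1.15 = 1.072. A nominal 95% interval would then cover about 100 − 6.8 = 93.2%. If ρ = 0, or if no sibling sets enrol, D = 1 and nothing is lost.

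**5. Check by simulation.** Unadjusted t-tests with 100 infants per arm (20,000 runs per setting) rejected in 5.8%, 6.5% and 8.2% of runs for the last three rows, close to the formula.

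**6. Consequence for the later trial.** If that trial also allocated siblings together, the same range of D would move 1498 to between 1498·1.01 ≈ 1513 and 1498·1.28 ≈ 1918. The upper end is probably too high for NEC, where the correlation is likely to be lower than for growth.

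**The case against.** **Silence is not a statement of independence.** A reader might infer that the plan declares infants independent. It does not. It names model families and an open list of covariates, and it says nothing about the variance estimator. A SAP that is not shown could add a family term. That stands as a limit on the claim, but it does not remove the point. The article goes into enough detail to name the models, the stratification variable, the competing-risk analysis and imputation, and it carries SGA into the models. Followed as written, those models ignore joint allocation.

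**There is no confirmatory test.** A reader might also infer that the trial's false-positive rate breaches 5%. The documents do not support that reading. The 0.05 level is stated only for the hypothetical later trial, the pilot reports intervals and calls its results preliminary, and the proceed criteria in Table 3 concern consent, recruitment and incomplete datasets. The harm is to interval width. The error rates above only express its size.

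**The size is assumed.** This also stands. Adjusting for gestational age, which siblings share, lowers the residual correlation, and for a rare binary outcome such as NEC it is probably lower again. At the low end the effect is negligible.

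**Two further inferences do not hold.**
- Unit practice varies ("The units may choose to individualise the fortification level according to the amount of protein"), so it is tempting to say that leaving unit out of the models loses part of the randomisation structure. Stratification is by SGA only, so unit is not part of that structure. Omitting it costs precision, not validity.
- The definition of the stratum, "where SGA is defined as a birth weight z-score less than two standard deviations", read literally would cover about 97.7% of a reference population. The term small-for-gestational-age makes the intended direction plain, so this is a missing minus sign, unrelated to sibling clustering.

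**Conclusion.** The point holds as a should-fix. For multiple births the family is the randomised unit, and the named models do not account for it. The direction is certain whenever siblings' outcomes correlate positively: the intervals are too narrow. The size is small to moderate and rests wholly on the assumed share of twins and the assumed correlation. It is most credible for growth and laboratory markers and least for NEC. The finding does not undermine the pilot's feasibility criteria or any formal test. It affects how precisely the pilot appears to estimate differences, and what it can hand on to the planning of the later trial.

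**What to change.** State in the Analysis section that the family is the randomised unit for multiple births and that every between-arm comparison accounts for it:
- **Continuous outcomes:** a family random intercept or GEE.
- **Binary outcomes, Cox and Fine–Gray models:** family-clustered robust variance.
- **Multiple imputation:** keep the family identifier in the imputed datasets.
- **Reporting:** give the number of sibling sets and the within-family correlation for the main outcomes, and say that 1498 assumes independent infants, so that the later trial can allow for siblings.

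Separately, as a minor wording correction, put the minus sign into the SGA definition.

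The cost is modest. Allocation through the first-born already requires sibling sets to be identified, although the article does not list a family identifier among the data collected, so its presence in the database should be confirmed. Intervals will be slightly wider. At 6% incidence only about 200·0.06 = 12 NEC cases are expected, so clustered variance for NEC may be unstable. That limitation should be stated alongside the NEC estimate.
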